### Data Processing

#### Gait analysis data

The kinematic data, the kinetic data and the plantar pressure will be processed by using Nexus (Vicon, Oxford, UK) software (Maastricht) or Qualisys Track Manager (Qualisys, Gothenburg, Sweden) software (Glasgow) and saved in the C3D format.

Kinematic and kinetic measurements will be used as an input for the inverse dynamic model and to validate the forward dynamic model. The dataset of one healthy subject will be used to develop the first model. Afterwards the datasets of the other healthy subjects will be used to refine the initial model, develop kinematic and kinetic rules and a morphing-based scaling facility so the models can be personalised. After the development of the morphing algorithm the combination of this algorithm and the two models will be used to predict the effect of insoles.

Data from the foot assessments in combination with the 3D surface scans will be processed to develop an algorithm for personalisation of the models with a non invasive, low-end method. It is intended to investigate if an algorithm can be developed to drive the musculoskeletal model directly from plantar pressure measurements, allowing the kinematic parameters of the lower extremities to be determined without the need for a full motion capture system.

#### Imaging data

CT data will be segmented into the individual bones of the foot using Mimics (Materialise, Leuven, Belgium) image processing software. The CT-data will be used to compute the joint axes of the foot, by correlating the positions of the bones in the various positions. The loaded CT-data in combination with the pressure measurement will be used to gain insight in the soft tissue characteristics of the foot. Insertion and via points will be identified from partial segmentation of the MR data and described as co-ordinates on the bones segmented from the CT data. Insertion points will be defined as the centre of the area of insertion.

### Data Analysis

Initial validation of the inverse dynamic model will be carried out by visual inspection of predicted and measured (via EMG) muscle timings. Formal validation of both models will be carried out by comparing plantar pressure measurements taken during gait analysis to those predicted by the forward dynamic model. Intraclass correlation coefficients (ICC_2, k_) will be used to compare peak and average pressures at the hallux, the lesser toes, each of the metatarsal heads, the midfoot region, and the lateral and medial heel. Future studies will investigate the validity of the models for predicting biomechanical changes induced by orthoses.

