**Methods/Design:**

Functional and anatomical datasets will be collected in a multicentre study from 10 healthy participants and 15 patients requiring orthotic devices. The patient group will include individuals with metarsalgia, flexible flat foot and drop foot.

Each participant will undergo a clinical foot function assessment, 3D surface scans of the foot under different loading conditions, and detailed gait analysis including kinematic, kinetic, muscle activity and plantar pressure measurements in both barefoot and shod conditions. Following this each participant will undergo computed tomography (CT) imaging of their foot and ankle under a range of loads and positions while plantar pressures are recorded. A further subgroup of participants will undergo magnetic resonance imaging (MRI) of the foot and ankle.

Imaging data will be segmented to derive the geometry of the bones and the orientation of the joint axes. Insertion points of muscles and ligaments will be determined from the MRI and CT-scans and soft tissue material properties computed from the loaded CT data in combination with the plantar pressure measurements. Gait analysis data will be used to drive the models and in combination with the 3D surface scans for scaling purposes. Predicted plantar pressures and muscle activation patterns predicted from the models will be compared to determine the validity of the models.

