#### Inverse dynamic model

Standard gait analysis and inverse dynamic models of the lower extremity consider the foot as a single rigid segment. Some models have been developed that describe the foot in more detail, however to the authors' knowledge no kinematic model has attempted to describe all 26 bones. The proposed kinematic model is scalable and parametric and will integrate into the existing AnyBody whole body musculoskeletal model (Figure 1). The model will contain all of the ligaments and muscles of the foot and ankle. By combing the inverse dynamic modelling with an optimisation algorithm the model will provide insight in function of the foot and leg muscles during gait.

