#### Electromyographic measurements

All parts of the protocol relating to surface EMG measurement will be carried out in accordance with the guidelines produced by the Surface Electromyography for the Non-Invasive Assessment of Muscles (SENIAM) project [20]. These guidelines cover the location and orientation of electrode placement, skin preparation and signal tests for each muscle.

Trigno wireless EMG systems (Delsys Inc, Boston, MA) will be used to collect the EMG measurements at both centres. The electrode units will be attached to the following muscles: tibialis anterior, gastrocnemius medialis, gastrocnemius lateralis, soleus, peroneus longus, vastus lateralis, rectus femoris, and biceps femoris. Signals from each muscle will be checked in real time using EMGworks software (Delsys Inc, Boston, MA) while performing the exercises described in the SENIAM guidelines.

Reference measurements will be taken for each muscle in the form of maximal voluntary isometric contractions (MVICs). Measurements will be recorded for five seconds in total with the participant being asked to gradually build up the force they apply over the first two seconds, and maintain their maximum effort for the remainder of the contraction. Each contraction is repeated three times in a non-consecutive randomised order with at least one minute recovery time between exercises.

For the MVIC and gait components of the testing, EMG signals from the Trigno sensors will be recorded through the analogue channels of QTM or VICON software at a frequency of 2400 Hz.

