A driving input of the models that will be developed in this study is the kinematic data. This data is acquired by a set of skin mounted markers. Markers are positioned on bony-landmarks, taking into account the influence of muscles, tendons and ligaments on skin motion. Previously reported bone pin studies show the distinction between the movements of the skin markers and the bones [33]. This distinction has two causes: soft tissue movement [34] and the rigid body violation [35]. The latter point is solved by introducing a 26 segment model. The problem of soft tissue movement is partially addressed by performing loaded CT with radio-opaque markers and having the option to include direction dependent weighting factors in the AnyBody model. A bone pin study involving all bones would be difficult due to the small size of the bones. In addition, the confounding effect of this invasive method on the motion pattern of gait is not known.

Validation of the models is partly performed by comparison of the muscle activity patterns predicted by the inverse dynamic model to those recorded during gait. EMG can be acquired by surface electrodes or by intramuscular measurements. Both methods have advantages and disadvantages. In this study surface EMG is used to minimise the influence of the measurements on normal gait as EMG is not used as an input for the model, only as a validation tool.

During the motion analysis force measurements are performed in 3D by a force plate and in one dimension by the plantar pressure plate. The force plate measures a global force vector of the ground reaction force, averaged in space. A pressure plate measures the individual vertical component of the ground reaction force over the full plantar surface. Ideally these measurements should be combined, yielding a high resolution measurement of three dimensional force vectors. Attempts have been made to develop this type of device, however no suitable and validated system is currently commercially available.

Weight bearing CT scans are performed with approximately 50% body weight. This is lower than would be encountered during normal gait, however the restrictions of the scanner mean that the participant needs to be in a sitting position so that the full foot and ankle can be imaged [36]. Commean et al [8] have demonstrated the reliability of weight-bearing CT in a sitting position.

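### The inverse model's muscle predictions are checked directly only by eye, yet plantar pressures from the forward model are said to validate both models formally

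*Protocol article*

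**What the plan says.** The Data Analysis section of the protocol article sets out two validation steps. For the inverse dynamic model: "Initial validation of the inverse dynamic model will be carried out by visual inspection of predicted and measured (via EMG) muscle timings". Then, for the pair: "Formal validation of both models will be carried out by comparing plantar pressure measurements". The predictions in that second comparison come from the forward dynamic model alone. The single statistic named is ICC(2,k), which "will be used to compare peak and average pressures at the hallux, the lesser toes, each of the metatarsal heads". Pressure under the midfoot and under the two sides of the heel is treated in the same way.

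Other sections give muscle activity a larger part. The Abstract says: "Predicted plantar pressures and muscle activation patterns predicted from the models will be compared to determine the validity of the models". The Discussion says: "Validation of the models is partly performed by comparison of the muscle activity patterns predicted by the inverse dynamic model to those recorded during gait", and adds that EMG is kept out of the model inputs and serves validation alone.

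On scope, the Inverse dynamic model section says: "The model will contain all of the ligaments and muscles of the foot and ankle". It obtains muscle function by adding an optimisation algorithm to the inverse dynamics. The Electromyographic measurements section lists eight muscles recorded at 2400 Hz, with maximal voluntary isometric contractions (MVICs) taken three times each as a reference. The Models section explains that an inverse model can supply the torques or muscle forces that a forward model needs. It treats combining the two models as something the shared dataset makes possible.

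**The concern.** Muscle activation is the inverse model's own prediction, and EMG is the one measurement collected to test it. The article assigns that test to visual inspection of timings, and does not say how close is close enough or what result would count against the model. It then uses the word formal for a comparison that involves only the other model's output.

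What is at stake is the conclusion that can be drawn. The Discussion makes a clinical trial of model-designed orthoses depend on successful validation. On the inverse side, the stated plan gives no direct quantitative basis for that decision, while its wording would let a good pressure ICC be reported as covering both models.

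**Working it through.** The plan states no figure to reproduce here. The check is which prediction is set against which measurement.

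**1. The comparisons that the article names**

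| Prediction | Compared with | Measure of agreement | Section |
|---|---|---|---|
| Inverse model: muscle timing | EMG | none (by eye) | Data Analysis |
| Forward model: plantar pressure | measured plantar pressure | ICC(2,k) | Data Analysis |
| Forward model | kinematic and kinetic data | none named | Gait analysis data |

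None of the three rows is a quantitative comparison of the inverse model's muscle predictions. The kinematic and kinetic data cannot supply one, because the Gait analysis data section makes them inputs to the inverse model.

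**2. Count of quantities with an agreement statistic**

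- Pressure regions: hallux 1 + lesser toes 1 (taken as one region) + metatarsal heads 5 + midfoot 1 + heel 2 = 10.
- Peak and average for each: 10 × 2 = 20 quantities with an ICC.
- Recorded muscles with an agreement statistic: 0 of 8.

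**3. Can pressure reach the inverse model indirectly?** Only if the inverse model's torques or muscle forces drive the forward model in the run whose pressures are compared. The Models section says this can be done and calls a combination of the models a possibility for a final application. Neither that section nor Data Analysis fixes it for the validation run.

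**4. If the models are linked, does pressure agreement verify the muscles?** Write the net moment at a joint as M = Σ rᵢFᵢ, with moment arms rᵢ and muscle forces Fᵢ. Take two muscles crossing that joint, raise F₁ by d/r₁ and lower F₂ by d/r₂. The change in M is r₁(d/r₁) − r₂(d/r₂) = d − d = 0. Different force patterns therefore give the same net moment, and the optimisation selects one of them. A forward run with the same net moments can give similar plantar pressure under any of these patterns. This is general mechanics, not a statement in the article, but it is why an optimisation is needed at all.

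**5. Coverage of the EMG.** Of the eight muscles, vastus lateralis, rectus femoris and biceps femoris do not cross the ankle, so 8 − 3 = 5 do: tibialis anterior, both gastrocnemius heads, soleus and peroneus longus. None is an intrinsic foot muscle, although the model is to contain all foot and ankle muscles.

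**6. Data already planned.** Per participant: 8 muscles × 5 trials × 2 conditions (barefoot, shod) = 80 muscle-trial recordings. Over 25 participants: 80 × 25 = 2000 at most. This is an upper count of correlated recordings, not a sample size. The article does not commit to inverse-model predictions for every participant in both conditions, and the healthy datasets are also used to build and refine the models.

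**The case against.** The strongest reply has four parts.

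- **Silence in a condensed article proves little.** The visual step is called initial, and the Abstract and Discussion speak of activation or activity patterns, so a fuller EMG comparison may be set out elsewhere. This stands in part. A reader might infer that EMG amplitude goes unused, but the article says nothing about EMG processing, so that inference is not supported. The reply does not rescue the validation sentences, though. The article itself names visual inspection for one model and assigns the formal step for both to pressure, so any later plan with a proper EMG analysis would have to change that wording.
- **The models are described as linked, so pressure tests the chain.** This stands as a qualification. If the validation run is linked, the pressure ICC is an indirect test, and it would be wrong to say that the inverse model escapes quantitative testing altogether. The link is not fixed, and step 4 above shows what it would leave untested.
- **Nothing is said about who inspects.** A reader might infer unblinded inspection by the model builders that cannot fail. The article states neither who looks nor whether they are blinded. What can be said is that no failure criterion is given.
- **This is a feasibility study whose primary aim is data collection, and the choice of surface EMG is discussed.** Both are true and limit the severity. The Discussion justifies surface over intramuscular recording, but it does not limit the validation claim to the muscles that surface EMG reached.

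**Conclusion.** The concern holds as a weak stated method joined to an over-broad claim. As written, the inverse model's muscle predictions receive a visual check of timing with no agreement statistic and no criterion, while 20 forward-model pressure quantities carry the formal claim for both models. Good pressure agreement would support the forward model, or the linked chain if the run is linked. It would not support individual muscle predictions, and no EMG comparison planned here can support predictions for intrinsic foot muscles.

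The conclusion rests on the article's own Data Analysis wording and on the general point that an optimisation chooses among muscle-force patterns with equal net moments. The size of any error in the muscle predictions cannot be estimated from the document. Given the exploratory design, this should be changed but is not fatal. It matters mainly because the next trial depends on the validation result.

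**What to change.** **Analysis.** For each of the eight recorded muscles, compare predicted activation with the MVIC-normalised EMG envelope over stance. Stance is the right window because the Gait analysis section says measurements are collected in that phase; percentages of the full gait cycle would not fit. Report:

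- onset and offset differences, in ms or % of stance, with limits of agreement;
- one envelope agreement measure, such as RMSE or cross-correlation, summarised per participant so that repeat trials are not counted as independent;
- a criterion, stated beforehand, for what counts as acceptable agreement.

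Fix the predictions before they are compared with the EMG. Signals are checked in real time at acquisition, so the freeze applies to the comparison and not to any sight of the EMG.

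**Wording.** In Data Analysis, say that the plantar-pressure ICC formally validates the forward model, or the linked model if inverse output drives the validation run, and state which applies. Say that the inverse model's muscle predictions are validated only for the eight measured muscles, none of which is intrinsic to the foot.

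**Cost.** A little more analysis and a few changed sentences, with no new data. The downside is that weak agreement may become visible and that predictions for unmeasured muscles must be labelled as unvalidated.

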#### Forward dynamic model

The forward dynamic model is a combined multibody and FE approach. Bones, joints, ligaments and muscles are defined as multibody elements. This multibody model is surrounded by a freeform FE sheet, representing the skin. The soft tissue characteristics are implemented by loading functions that connect the sheet to the multibody elements. This combination leads to a computationally less complex model compared to a full FE model of the foot and ankle. This reduction could be improved by a full multibody representation of the ankle-foot complex, however in this model computation of the plantar pressure would be impossible. In the proposed model this is solved by a FE mesh representing the plantar surface, leading to the possibility of performing a dynamic simulation to compute the deforming plantar surface.

An existing model (Figure 1) has previously been developed from a combination of data from a post-mortem human subject and information derived from existing literature [15]. The generation of one complete dataset leads to a consistent model. Beyond this, the generation of datasets from several subjects creates the possibility of scaling the model. This scaling will be extended for patients requiring foot and ankle orthoses.

The overall aim of this work is to develop detailed and accurate biomechanical models of the foot and ankle which can be used to inform the design of foot and ankle orthoses by predicting the biomechanical effects of the device.

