### Clarification of sample size

The exploratory nature of this study makes it difficult to calculate power requirements for statistical purposes. Therefore, a pragmatic approach has been taken with the number of subjects chosen by the opinion of experts to cover a broad scope of variation of foot problems. A broad range of subjects in terms of foot size, age, BMI, will be included for development of scaling methods and to test the validity of the models.

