#### Testing

A static trial will be recorded with the participant in a relaxed standing pose in the motion capture area. The participant will then be asked to walk barefoot at a self selected speed along the motion capture area such that their right foot strikes the centre of the pressure plate. Five successful walking trials will be recorded. This will then be repeated for the shod trials.

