Despite these limitations, the protocol will produce unique datasets consisting of detailed anatomic and dynamic measurements. These will be used to develop scalable biomechanical foot models to improve understanding of foot function and to attempt to predict the effect of foot and ankle orthotic design so that the design of these devices can be optimised prior to manufacture, potentially removing some of the variability in form and function that is seen with currently prescribed devices. Driving the models using dynamic plantar pressure rather than kinematic measurements could make this approach particularly useful and accessible for clinicians, avoiding the cost and time associated with full motion capture analysis. If validation of the models is successful, the next step will be to run a clinical trial to test if the use of the model for the development of foot and ankle orthoses leads to improved efficacy.

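### The validation uses the average-measures ICC(2,k), which describes the mean of model and measurement, although the model's prediction is meant to be used alone; ICC(2,1) is the matching form

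*Protocol article*

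**What the plan says.** The Data Analysis section describes two checks. The first is a visual comparison of predicted muscle timing with EMG. The second is the formal one: "Formal validation of both models will be carried out by comparing plantar pressure measurements". The comparison is specified as "comparing plantar pressure measurements taken during gait analysis to those predicted by the forward dynamic model", and the statistic as "Intraclass correlation coefficients (ICC_2, k_) will be used to compare peak and average pressures", by foot region. The section does not define k, gives no reason for the average-measures form, and names no other measure of agreement.

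Three other places bear on the choice:

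- The Forward dynamic model section says the models are to be "used to inform the design of foot and ankle orthoses by predicting the biomechanical effects of the device". The prediction is the working output.
- The Testing section says "Five successful walking trials will be recorded" barefoot, and the same is then repeated shod.
- The Discussion ties a next step to the result: "If validation of the models is successful, the next step will be to run a clinical trial".

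**The concern.** In the usual notation for intraclass correlations, the first index gives the model (2 = two-way random effects, absolute agreement). The second says whether the coefficient refers to one rating (1) or to the mean of k ratings (k). The ratings here are the predicted and the measured pressure in the same region of the same foot. ICC(2,k) therefore asks how reliable the average of prediction and measurement would be.

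That average has no role in the project. A designer using the model would have the prediction and would act on it. The useful question is how closely one prediction agrees with the measurement, which ICC(2,1) answers. The average-measures coefficient is the larger of the two whenever the single-measure value lies strictly between 0 and 1. A reader who takes it as agreement between model and measurement will think the model better than it is. This is the only quantitative validation statistic the article names, and a further trial is made to depend on successful validation.

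**Working it through.** The article states no ICC value, threshold or power, so there is no figure of its own to reproduce. The check is algebraic, with the single-measure ICC varied over an assumed range.

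**Inputs**

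- Two sources compared, model and measurement, hence k = 2 (inferred from Data Analysis; k is not defined there).
- Five walking trials per condition (Testing), the only other number that could be taken for k.
- Single-measure ICC: not given, so a range is assumed.

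**Formulas.** With mean squares for subjects (MSR), sources (MSC) and error (MSE), and n subjects:

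- ICC(2,1) = (MSR − MSE) / [MSR + (k − 1)MSE + k(MSC − MSE)/n]
- ICC(2,k) = (MSR − MSE) / [MSR + (MSC − MSE)/n]

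For k = 2, write A = MSR − MSE and B = MSR + (MSC − MSE)/n. The first denominator, MSR + MSE + 2(MSC − MSE)/n, equals 2B − A. So ICC(2,1) = A/(2B − A) and ICC(2,2) = A/B. This gives the Spearman-Brown relation with r = ICC(2,1):

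- ICC(2,2) = 2r/(1 + r), and in reverse r = ICC(2,2)/(2 − ICC(2,2))
- gap = 2r/(1 + r) − r = r(1 − r)/(1 + r)

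On one simulated data set with a systematic offset between the sources, ICC(2,1) was 0.784 and ICC(2,2) was 0.879; the formula gives 2 × 0.784/1.784 = 0.879.

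**Results, k = 2**

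| Single-measure ICC(2,1) | Reported ICC(2,2) | Gap |
|---|---|---|
| 0.20 | 0.33 | 0.13 |
| 0.33 | 0.50 | 0.17 |
| 0.40 | 0.57 | 0.17 |
| 0.50 | 0.67 | 0.17 |
| 0.60 | 0.75 | 0.15 |
| 0.80 | 0.89 | 0.09 |
| 0.90 | 0.95 | 0.05 |

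The gap is greatest at r = √2 − 1 = 0.414, where it is 0.414 × 0.586/1.414 = 0.17. A reported 0.75 means 0.75/1.25 = 0.60 for a single prediction; a reported 0.90 means 0.90/1.10 = 0.82.

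**Could k mean the five trials?** Averaging the five measured trials gives one measured value per participant, set against one predicted value. That is still a single-measure comparison. If the coefficient were stepped up with k = 5, the difference would be larger: 0.50 would become 5 × 0.50/(1 + 4 × 0.50) = 0.83, and 0.375 would become 1.875/2.5 = 0.75.

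**The case against.** **ICC(2,k) is not a biased estimate.** It estimates a different quantity. With k = 2 the two forms convert one to one, so nothing is lost and the ranking of models or regions does not change. This stands. The fault is in what the coefficient will be taken to mean, and the conversion helps only a reader who knows that k is 2, which the article does not say.

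**k may be loose notation for trial averaging.** The authors may have meant that a five-trial mean is entered for the measurement. If so, the fault is in the notation, but the single-measure form is still the one to name and report.

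**No decision depends on the value.** A reader might infer that a model with mediocre agreement would be declared valid and carried into a trial. The documents do not support this. No ICC threshold is stated, and any probability of passing would need an invented cut-off. Data Analysis also leaves validity for orthosis-induced changes to future studies. The objection stands, and it limits the point to interpretation.

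**Mixing groups.** A reader might also infer that combining healthy and patient feet inflates the coefficient further. Data Analysis does not say which participants enter the ICC or that the groups are combined in it. The pooling in Study Design refers to data from the two centres being brought together for model development. Any size for this effect would rest on an assumed group difference, so it is not part of the point.

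**This is a pilot.** The sample size section says "The exploratory nature of this study makes it difficult to calculate power requirements for statistical purposes", and the Discussion gives data collection as the primary aim. That bears on severity. It does not justify a coefficient that describes a quantity no one will use.

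**Conclusion.** The average-measures form does not match the intended use and should be replaced by ICC(2,1). As planned, the coefficient will exceed single-prediction agreement by up to about 0.17: by 0.13 to 0.17 for single-measure values from 0.20 to 0.60, and by 0.05 to 0.09 for values from 0.80 to 0.90.

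These sizes assume k = 2, which follows from the comparison described but is not stated. Where in the range the study would fall cannot be known from the article. The consequence is an over-favourable reading of what counts as successful validation, not the breach of a decision rule. The severity is should-fix.

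**What to change.** In Data Analysis, replace ICC(2,k) with ICC(2,1), absolute agreement, with a 95% confidence interval for each region and for both peak and average pressure. State that the measured value entered is each participant's mean over the five trials.

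The interval should allow for a systematic difference between model and measurement. For an assumed ICC(2,1) of 0.75 with all 25 participants ("10 healthy participants and 15 patients requiring orthotic devices"), it runs from about 0.51 to 0.88 if there is no such difference, and from about 0.26 to 0.91 if a tenth of the total variance is systematic.

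Also report the mean difference and limits of agreement in pressure units for each region, because an ICC does not show the size of the prediction error.

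The cost is two sentences and no new data. The downside is that the reported coefficients will be lower. Reporting the groups separately, or tying success to a lower confidence limit, is a matter of preference and is not needed to mend this point.
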